### Patient and public involvement

We commit to fostering a collaborative and inclusive approach to maximize the impact of our intervention by actively involving beneficiaries and stakeholders. We have actively engaged with representatives of women of reproductive age at the formative study sites and stakeholders involved in MCH across multiple levels, including NMCHC, PHDs, ODs, HCs, VHSGs, and NGOs, to conduct a comprehensive gap analysis and develop protocols and tools. This engagement remains a priority as we progress through the study’s implementation, evaluation, and dissemination phases. To ensure their ongoing involvement, we will extend invitations to representatives from each stakeholder group to join a project steering committee. This committee will be pivotal in guiding the study’s direction and decision-making. Meetings of the project steering committee will convene every 3 months to assess project progress, gather feedback, identify potential issues, and advise on any challenges that may arise throughout the project’s lifecycle.

### Anticipated risks and benefits to human subjects

There are no significant perceivable risks to participating in this study, aside from the inconvenience of taking the time to answer questions for the beneficiaries and the time to attend the *i-MoMCARE* mobile application and web interface training course for VHSGs and HC staff. Additionally, we foresee the potential psychological distress to be minimal. There are no direct benefits for the participants; however, this study will contribute to integrating digital health technology to bridge gaps and ultimately improve MCH services in rural Cambodia. However, we anticipate several potential risks that we can address. For instance, if the respondents incur any morbidities during the interview, they must be accompanied to the nearest health facility, whether in the intervention or control arm. Besides, if domestic violence occurs during the data collection, the interviewers will stop the interviews and call local authorities, such as the village chief, to resolve the problem. In addition, VHSGs will observe signs of aggression or violence in the participants to avoid potential harm.

### Compensation and incentives

The VHSGs and HC staff in the intervention arm will receive a monthly stipend of USD 15 and USD 20 during the pilot and the intervention period. Participants in IDIs, KIIs, FGDs, and household surveys will receive USD 2.5 for each interview.

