## Abstract

**Background:**

The Government of Cambodia established the village health support groups (VHSGs) in 2003 to facilitate primary healthcare activities, including maternal and child health (MCH) services. However, VHSGs face several challenges that hinder them from performing optimally, including a lack of regular structured training and remuneration and limited and inconsistent support and supervision from the health centers (HCs). This implementation research aims to develop, implement, and evaluate a digital health intervention to improve the performance of VHSGs through better support and supervision and increase the MCH service coverage in rural Cambodia.

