**Methods:**

i-MoMCARE, a two-arm cluster randomized controlled trial, will be conducted between 2022 and 2025. Five operational districts (ODs) have been randomized to an intervention arm and the other five ODs to the control arm. The intervention will last for 24 months. Around 200 VHSGs in the intervention arm will be equipped with a mobile application as a job aid and 20 HC staff with a web interface to improve support and supervision of VHSGs. The potential beneficiaries will include pregnant women, mothers, and children under 2 years old. We will measure the outcomes at baseline and endline. The primary outcomes will consist of a composite MCH index constructed from maternal and newborn care indicators, child immunization, and treatment of under-two children. Secondary outcomes will include coverage of selected MCH services. We will conduct the intention-to-treat and per-protocol analyses. We will conduct qualitative interviews with selected beneficiaries and stakeholders to evaluate the intervention’s acceptability, feasibility, and scalability. We will also conduct a cost-effective analysis using decision-analytic modeling incorporating a societal perspective that explores different time horizons, intervention effects, and when scaled up to the national level.

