#### Village health support groups (VHSGs)

VHSGs are usually elected by their community members and based in the community under the HC’s coverage. VHSGs are community-based health volunteers with limited education; some do not even have education beyond primary school [28]. They will be the primary implementers of the *i-MoMCARE* intervention. They will communicate with the beneficiaries directly to narrow the gap in the knowledge of maternal, newborn, and child health and refer pregnant women and children to the nearest HC when necessary. One HC serves approximately 10 villages, and one village has one or two VHSGs serving 100 households or more. We will select 20 VHSGs (two VHSGs per village) for each HC in the intervention and control arms (200 from each arm). All VHSGs in the intervention and control arm will undergo MCH-related refresher training before the intervention. Only VHSGs in the intervention arm will be equipped with the mobile application.

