**Fig. 4 Fig4:**
[figure not shown]
Map of the study sites (each color represents a paired province)

The designated HC staff will receive a web interface application as their job aid for supervising VHSGs, including real-time information about VHSGs’ performance in the form of process indicators and MCH service coverage. The web interface will provide timely information and tools for HC staff to facilitate the monitoring and supporting of VHSGs by supporting HC staff in their daily tasks, such as high-risk patient tracking, low-supply inventory alerts, supply chain management, electronic health records, vital events tracking, and automatic calculation of performance-based incentives and motivation for VHSGs. Two VHSGs from each of the 100 villages (a total of 200 VHSGs) will receive the mobile application connected to their respective HC in the intervention arm. The mobile application will provide job aid to VHSGs to enroll eligible women and children, schedule and review home visits, report outcomes of pregnancies, conduct home-based newborn care, follow-up visits of complicated cases, and report information about deaths, emergencies, migrations, referrals, and services, by logging into the application installed on the mobile devices every day except for Sundays. The mobile application will also help with behavioral change communication via brief educational videos about danger signs in pregnancies and newborns to be shown to pregnant women. At endline, we will conduct a qualitative acceptability and feasibility assessment of the intervention by conducting IDIs with VHSGs and HC staff from the intervention arm and FGDs with six to eight eligible pregnant women and mothers of under-two children in the five HCs selected for the IDIs. Approximate numbers of IDIs and FGDs are shown in Table 4. The interviews will be conducted until saturation of the information is reached.

**Table 4 Tab4:** Qualitative interview at the endline

Participant	In-depth interview	Focus group discussion
Health center staff	10	
Village health volunteer group	10	
Pregnant women and new mothers		5^a^
Total	20	5

^a^With 6–8 women in each group

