##### Control arm

As discussed in the study design, HCs in the control arm will be randomly selected from their ODs. The randomization process will be similar to those in the intervention arm. All villages under the HC’s catchment areas in the control arm will continue to receive MCH standard care provided by the government and NGOs and facilitated by VHSGs. VHSGs in the intervention and control arms will receive refresher training on maternal, neonatal, and childcare to avoid ethical issues that may arise and ensure that any change in outcomes in the intervention arm is due only to the *i-MoMCARE* intervention.

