### Strengths and limitations

A considerable strength of this study is the cluster randomized controlled trial design using the innovative digital health technology successfully implemented and evaluated in the tribal communities in India [56]. This application does not require technology integration into the national platform, as this study will fully adapt this innovative approach. Additionally, the population under the technology coverage is substantially smaller than that in India, suggesting no critical challenges to this application. On top of that, the implementation will be supported by the national program, which spearheads the nationwide implementation of MCH service provision.

Despite these strengths, this study has several technical and operational challenges and limitations. On the technical side, a low level of education and digital literacy among VHSGs could be a challenge, while different mobile network providers in other geographical locations are another. On the operational side, we anticipate a high turnover rate among VHSGs due to the voluntary nature of their work, the demand for household chores, and other competing job opportunities in the community. The local partners—UHS and NMCHC—will address these challenges by ensuring the minimum level of education of nine years, selecting mobile network providers based on their geographical presence, and providing constant motivation and support to VHSGs.

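### A monthly stipend is stated for the intervention arm only, so the trial estimates the effect of a package and cannot attribute it to the digital technology

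*Protocol article*

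**What the plan says.** All places are in the protocol article.

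- **Compensation and incentives:** payment is set out as "The VHSGs and HC staff in the intervention arm will receive a monthly stipend of USD 15 and USD 20". It covers both the pilot and the main trial. The control arm is not mentioned.
- **Abstract, Methods:** "The intervention will last for 24 months".
- **Control arm:** villages "in the control arm will continue to receive MCH standard care provided by the government and NGOs". VHSGs in both arms get refresher training, partly to "ensure that any change in outcomes in the intervention arm is due only to the" i-MoMCARE intervention.
- **Village health support groups (VHSGs):** the stated difference between arms is that "Only VHSGs in the intervention arm will be equipped with the mobile application".
- **Background, Discussion, Conclusion:** i-MoMCARE is described as a digital health intervention, and the trial as a test of phone and web applications.
- **Abstract, Background:** VHSGs face challenges, "including a lack of regular structured training and remuneration".
- **Health center staff:** late payment is listed among the reasons why some VHSGs function poorly.
- **Strengths and limitations:** "we anticipate a high turnover rate among VHSGs due to the voluntary nature of their work", among other reasons. Unequal payment is not listed as a limitation.
- **Phase 2: Cluster randomized controlled trial:** the web interface includes "automatic calculation of performance-based incentives and motivation for VHSGs".

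**The concern.** The abstract names missing training and missing remuneration together as barriers to VHSG performance. The design gives the training to both arms and states the remuneration for one. By the protocol's own account, then, pay is a plausible active ingredient, and it comes with the app in every intervention cluster.

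At stake is how the result will be read. The Abstract, Discussion and Conclusion look forward to evidence on digital health technology, and the cost-effectiveness analysis will model national scale-up. If a positive result is reported as the effect of the technology, part or all of it may come from paying volunteers. Applying the trial effect to a roll-out without stipends would then have no support in the data.

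**Working it through.** **1. What differs between the arms**

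| Element | Intervention | Control | Source section |
|---|---|---|---|
| Refresher training | yes | yes | Control arm |
| Mobile app for VHSGs | yes | no | Village health support groups |
| Web interface for health center (HC) staff | yes | none stated | Phase 2 |
| Facilitator support | for users of the technology | none stated | i-MoMCARE facilitators |
| Site-coordinator feedback and meetings | yes | none stated | Health center staff |
| Monthly stipend | yes | none stated | Compensation and incentives |

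Training is stated as equal. The stipend and the app are both tied to arm. With two arms and complete overlap, neither intention-to-treat, per-protocol, difference-in-difference nor covariate-adjusted analysis can separate them.

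**2. Size of the payment difference**

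Inputs: USD 15 per VHSG and USD 20 per HC staff member each month (read in the order listed), 24 months, 200 VHSGs and 20 HC staff in the intervention arm.

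- Per VHSG: 15 × 24 = USD 360
- All VHSGs: 200 × 15 × 24 = USD 72,000
- Per HC staff member: 20 × 24 = USD 480
- All HC staff: 20 × 20 × 24 = USD 9,600
- Total: 72,000 + 9,600 = USD 81,600

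The pilot is left out; it takes place in another province.

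**3. Exposure of the primary outcomes**

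Two of the three primary outcomes record VHSG activity directly: at least two home visits in the first week, and danger-sign information given by VHSGs. The third is MCH-CI = 1/3 (1/4 APNC + 1/2 IMMU + 1/3 TREAT). Taking each term as the sum of its items, the weights are:

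- APNC item: 1/3 × 1/4 = 1/12 (four items)
- IMMU item: 1/3 × 1/2 = 1/6 (two items)
- TREAT item: 1/3 × 1/3 = 1/9 (three items)
- Check: 4/12 + 2/6 + 3/9 = 1

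Items that are acts of the VHSG are home visits in pregnancy (1/12) and oral rehydration therapy from VHSGs (1/9): 1/12 + 1/9 = 3/36 + 4/36 = 7/36, about 19%. Two further TREAT items concern families seeking care from VHSGs. Adding them gives 7/36 + 2/9 = 15/36 = 5/12, about 42%.

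**4. How much of the effect could be payment**

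The Sample size section assumes an effect of 13% on a 70% index. Read as percentage points (0.70 against 0.83, two-sided 5%, 85% power, unpooled variance), this gives 186.53 per arm. The design effect is 1 + 199 × 0.02 = 4.98, and 186.53 × 4.98 = 928.9, which reproduces the stated 929 per arm. So 13 points is the planned effect. The documents give no figure for the effect of pay alone. If neither component does harm, the stipend's share of those 13 points could be anything from 0 to 13, and the trial cannot narrow that range.

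**The case against.** The strongest reply is that the Control arm section attributes change to i-MoMCARE, not to the app. If the stipend belongs to i-MoMCARE, the sentence holds and the randomised contrast estimates what it should. Testing a package is normal in implementation research, and the protocol describes more than software: facilitators make field visits, coordinators give feedback, and the web interface calculates VHSG incentives. This stands in part. A reader might infer that the trial is confounded and its estimate invalid; the documents do not support that, because the package effect is validly estimated. But the protocol never names the stipend as a component, and it describes the intervention as digital.

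Other stronger readings also go too far:

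- **That control VHSGs are unpaid.** This is inferred from silence. Nothing is said about payments from government or NGOs, so USD 360 is the stated difference, not a proven gap.
- **That 42% of the index measures volunteer effort.** Two of the four items are worded as care-seeking by families; 19% is the firmer figure.
- **That fixed stipend and performance incentives contradict each other.** They can coexist. The protocol does not say whether both are paid.
- **That the stipend is left out of the costing.** Manpower under Cost-effectiveness analysis may cover it, and detail is deferred to a health economic analysis plan. However, the stipend is listed beside payments for interviews, and research costs are excluded, so its classification is open.
- **That paying control VHSGs would solve the problem.** It would cost about USD 72,000 and leave the HC staff stipend, facilitator support and coordinator feedback unequal. It would not isolate the technology.

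**Conclusion.** The point holds as a limit on attribution and should be fixed. Randomisation, the sample size and the package-level estimate are not affected. The protocol cannot support a technology-specific conclusion, because a component that it regards as relevant to VHSG performance is stated for one arm only and is not declared part of the intervention.

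The stated payment is about USD 81,600 over the intervention. The exposed outcomes are two primary outcomes outright and 7/36 of the third (up to 5/12 on the wider count). The share of any effect due to payment is not identifiable. This rests on three assumptions: control VHSGs get no equivalent stipend, the two amounts apply to VHSGs and HC staff in the order listed, and payment runs for the full 24 months.

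**What to change.** 1. Define the randomised intervention as the package: app, web supervision, facilitator and coordinator support, and monthly stipend. Restate the attribution sentence under Control arm, and the conclusions in the Abstract, Discussion and Conclusion, for that package. Add to Strengths and limitations that payment and technology cannot be separated.
2. State in the cost-effectiveness plan that the stipend, and any performance incentive, is a recurrent programme cost in the base case and in every scale-up scenario, not an excluded research cost. Do not apply the trial effect to a scenario without stipends.
3. State whether the performance-based incentives under Phase 2 are paid in addition to the stipend.

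These are changes of wording and model inputs. They need no new data and can be made after recruitment has started. The price is a narrower claim and possibly a less favourable cost-effectiveness ratio.

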## Discussion

Improving MCH services uptake and maternal, neonatal, and infant health are public health priorities in the Sustainable Development Goals [52]. Although the overall MMR and IMR in Cambodia have drastically declined over the last two decades, the rates among people living in rural areas remain disturbingly high [1]. As seen in other LMICs, urban versus rural disparities in MCH services access and uptake remain large in Cambodia. Mobile technology has been used to improve community-based health interventions to bridge the gaps [53, 54], along with adopting digital health innovations in solving other public health problems in the country [55].

Evidence from Modi and colleagues [18] suggests mHealth technology’s success in improving MCH services coverage and quality in hard-to-reach settings in rural Gujarat, India [18]. By fully adopting the technology, this study aims to test and implement mobile phone- and web-based applications in a rural Cambodian context using a cluster randomized controlled trial. Findings from this study will drive public health policy changes in Cambodia, while lessons learned may benefit other LMICs where digital health interventions can be advantageous. This study has come at the right time when Cambodia’s MOH has committed to developing digital health innovations in the country. The government has established the National Committee for Digital Health and is now forming the Department of Digital Health under the MOH.

### Strengths and limitations

A considerable strength of this study is the cluster randomized controlled trial design using the innovative digital health technology successfully implemented and evaluated in the tribal communities in India [56]. This application does not require technology integration into the national platform, as this study will fully adapt this innovative approach. Additionally, the population under the technology coverage is substantially smaller than that in India, suggesting no critical challenges to this application. On top of that, the implementation will be supported by the national program, which spearheads the nationwide implementation of MCH service provision.

Despite these strengths, this study has several technical and operational challenges and limitations. On the technical side, a low level of education and digital literacy among VHSGs could be a challenge, while different mobile network providers in other geographical locations are another. On the operational side, we anticipate a high turnover rate among VHSGs due to the voluntary nature of their work, the demand for household chores, and other competing job opportunities in the community. The local partners—UHS and NMCHC—will address these challenges by ensuring the minimum level of education of nine years, selecting mobile network providers based on their geographical presence, and providing constant motivation and support to VHSGs.

## Conclusion

This cluster randomized controlled trial aims to develop, implement, and evaluate the applicability and efficacy of the *i-MoMCARE* intervention to support VHSGs and HC staff in rural communities to increase the coverage of and access to MCH services in Cambodia. This trial is the first study using digital health technology to support community-based health volunteers providing MCH services in Cambodia. It will contribute to advancing digital health use in primary healthcare interventions, which remain in their infancy in LMICs. This study will contribute to Cambodia Digital Government Policy 2022–2035 in general and the HealthTeach Roadmap in particular. Lessons learned from this trial can inform digital health interventions for improving MCH in other LMICs.

## Trial status

Protocol version 1, April 7, 2023. The recruitment for intervention is expected to commence in June 2023 and will continue until May 2025.

## Data Availability

Not applicable.

## Abbreviations

ANC: Antenatal care
BMGF: Bill & Melinda Gates Foundation
CDHS: Cambodia Demographic and Health Survey
CEA: Cost-effectiveness analysis
CET: Cost-effectiveness threshold
CHEERS: Consolidated Health Economic Evaluation Reporting Standards
CONSORT: Consolidated Standards of Reporting Trials
CSES: Cambodia Socioeconomic Survey
DAC: Design, Analyze, and Communicate
DALY: Disability-adjusted life years
DPT: Diphtheria, pertussis, and tetanus
FGD: Focus group discussions
GDP: Gross domestic product
GEE: Generalized estimating equation
HC: Health center
ICC: Intra-cluster correlation
ICER: Incremental cost-effectiveness ratio
IDI: In-depth interviews
IMR: Infant mortality rate
i-MOMCARE: Innovative Mobile Technology for Maternal and Child Health Care
ImTeCHO: Innovative Mobile-phone Technology for Community Health Operations
IPV: Inactivated polio vaccine
ITT: Intention-to-treat
LMIC: Low- and middle-income countries
MCH: Maternal and child health
MMR: Maternal mortality ratio
MOH: Ministry of Health
NECHR: National Ethics Committee for Health Research
NMCHC: National Maternal and Child Health Center
NUS-IRB: National University of Singapore’s Institutional Review Board
NUS-SSHSPH: Saw Swee Hock School of Public Health of the National University of Singapore
OD: Operational district
OPV: Oral polio vaccine
PHD: Provincial health department
PNC: Postnatal care
RCT: Randomized controlled trial
SES: Socioeconomic status
SPIRIT: Standard Protocol Items: Recommendations for Interventional Trials
UHC: Universal health coverage
UHS: University of Health Sciences
UNFPA: United Nations Population Fund
UNICEF: United Nations Children’s Fund
VHSGs: Village health support groups
WHO: World Health Organization
YLD: Years lived with disability
YLL: Years of life lost
YLS: Years of life saved
